**Discussion:**

This trial aims to provide evidence on the combined use of LLINs and IRS for malaria prevention by answering the following research questions: Can the combined use of LLINs and IRS significantly reduce the incidence of malaria compared with the use of either LLINs or IRS alone? And is the reduced incidence justifiable compared to the added costs? Will the combined use of LLINs and IRS reduce vector density, infection, longevity and the entomological inoculation rate? These data are crucial in order to maximize the impact of vector control interventions on the morbidity and mortality of malaria.

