Evidence on the effect of the combined use of LLINs and IRS from community-based field trials is conflicting. Consequently, it is difficult to draw any conclusions on whether the combination of IRS and LLINs is beneficial against malaria compared to one of the interventions alone. A recent review indicated that only one of the four published randomized controlled trials showed additional protection against fighting malaria when the use of LLINs was combined with IRS, compared to either method alone [14]. A multi-intervention trial in Benin showed no significant reduction in clinical malaria in children under 5 years of age from houses sprayed with bendiocarb in combination with LLINs, compared to children in houses with LLINs alone [19]. Similarly, in The Gambia a combination of IRS using dichloro-diphenyl-trichloroethane (DDT) and universal coverage of LLINs showed no added protection against malaria among children of 6 months to 14 years compared to the universal coverage of LLINs alone [20]. By contrast, a recent cluster randomized controlled trial in Tanzania, where the usage of LLINs was less than 50 %, reported some evidence of added protection against malaria infection in children 6 months to 14 years from the combining of insecticide-treated nets (ITNs) and IRS with bendiocarb compared to ITNs alone [13]. Lines and Kleinschmidt [21] recently discussed the design issues in conducting studies involving the combination of malaria vector control interventions and recommended further evidence from well-designed trials.

Good evidence on the effectiveness, costs and cost-effectiveness of malaria interventions will provide important information for decision-making in policy formulation, the revision of existing policy and/or the selection of optimal packages of interventions. Since the cost of both LLINs and IRS is greater than the cost of either intervention alone [22], it is important to estimate and evaluate whether the potential extra protection gained by combining both interventions represents good value compared with the added costs. This is particularly important in countries in SSA, where a scarcity of resources is the main impediment to malaria control. A recent review of the evidence of the costs and consequences of large-scale vector control for malaria concluded that both LLINs and IRS are highly cost-effective vector control strategies even though the former method has been identified as more cost-effective than the latter [22].

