Several studies from Ethiopia have shown a high insecticide resistance in malaria mosquitoes, especially in relation to DDT, malathion, permethrin and deltamethrin [38–42]. DDT was the primary insecticide of choice for IRS in the country for a long time until it was replaced by deltamethrin in 2009. Unfortunately, resistance to deltamethrin was reported to be very high [38]. As a result, the National Malaria Control Program has adopted the use of bendiocarb and propoxur insecticides belonging to the carbamate family since 2012 [27, 43]. Currently, bendiocarb and propoxur are the primary insecticides of choice for IRS in Ethiopia. Bendiocarb and propoxur are carbamate insecticides evaluated and approved by the WHO Pesticide Evaluation Scheme, both of which have the potential to control pyrethroid-resistant mosquitoes [44].

This study aims to investigate the effect of combining LLINs and IRS with propoxur for the incidence of clinical malaria and the cost-effectiveness of the interventions against malaria and their effect on mosquito behavior, as compared to each intervention alone. The overall aim is to provide information for national and global policy-makers in their pursuit of improving malaria control by evaluating resource demands and the combined effect of both interventions on malaria. This protocol discusses the rationale for the choice of the interventions and describes the designs and methodological approaches being used to determine the effect of each intervention, in addition to evaluating the effect of the interventions.

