#### Secondary objectives

In the same study population, the secondary objectives of the trial are to:Estimate the costs of LLINs + IRS, LLINs or IRS alone compared to the current routine practice, and to evaluate the incremental costs, effects and cost-effectiveness of interventionsAssess whether LLINs + IRS reduce entomological parameters, i.e., human biting rates, mosquito resting density, longevity, sporozoite rates, and the entomological inoculation rate (EIR) inside houses compared with LLINs or IRS aloneDetermine whether LLINs + IRS improves the hemoglobin (Hb) concentration and reduces anemia among children under 5 years of age compared with children in LLINs or IRS alone

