### Study endpoints

The primary health outcome measure is malaria incidence determined by the detection of *P. falciparum* or *P. vivax* by rapid diagnostic tests (RDTs) in patients with a fever or having a history of fever within the previous 48 hours upon arrival at health posts by passive case detection (PCD). The sensitivity and specificity of the RDTs compared with the results of the light microscopy will be determined. The secondary health outcome measure is mean Hb concentration in children under the age of 5 years, which is measured using a portable photometer (HaemoCue®, Ångelholm, Sweden) at the end of each transmission season through community-based house-to-house visits.

The primary outcome measure of the economic evaluation is the total cost of the interventions. The secondary outcome measures are the direct and indirect costs of the intervention from both the provider and societal perspectives, which includes Disability- adjusted Life Years (DALYs) and the number of malaria cases averted by each intervention.

The primary entomological outcome measure is malaria transmission expressed as EIR, estimated as the mean number of sporozoite infective bites/person/year. The secondary entomological outcome measures are the mean number of *An. arabiensis*/light trap/night, and mean number of *An. arabiensis* in spray catches/night inside houses.

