The WHO age-adjusted cut-off for Hb will be used to classify anemia in children [71]. For children between 6–59 months of age, a normal Hb level is defined as Hb of 11.0 g/dl or greater and as mild at 10.0–10.9 g/dl. Moderate anemia is defined as children with an Hb level of 8.0–10.9 g/dl while severe anemia is defined as an Hb level of less than 8.0 g/dl. At a community level, a prevalence of anemia will be stated to be severe if over 40 % of the children are anemic (combining mild, moderate and severe) and moderate if the prevalence is 20–39.9 %. We will measure the weight and height of all children under the age of 5 years, and calculate the anthropometric indices such as weight for height, height for age, and weight for age. Both malaria and anemia prevalence data will be compared in the intervention and control clusters using multilevel mixed-effects logistic regression models, taking clustering effects into account.

Cost-effectiveness, expressed as an incremental cost-effectiveness ratio (ICER), will be calculated for each outcome and arm using standard DALY weights. The interventions will be ranked according to cost-effectiveness, whereas inequality in terms of health outcomes, will be measured by the Gini coefficient and the concentration index [72].

The agreement between the two mosquito collection methods, HLC and light traps, in assessing mosquito sampling efficiency will be calculated by a parametric approach based on an analysis of variance and simple graphical methods. Indoor and outdoor *Anopheles* densities will be compared among the study arms using a one-way analysis of variance (ANOVA) if data are normally distributed or using a Mann-Whitney *U* test if data are non-normally distributed.

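### The economic analysis ranks one ICER per arm with no fixed comparator, which does not answer whether the combination is worth its added cost over a single intervention

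*Protocol article*

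**What the plan says.** The Analytical plan gives the cost-effectiveness analysis two steps. Cost-effectiveness is "expressed as an incremental cost-effectiveness ratio (ICER), will be calculated for each outcome and arm using standard DALY weights", and then "The interventions will be ranked according to cost-effectiveness". Neither step names the reference arm for the ratio, a comparison between arms, or the removal of dominated options.

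Other methods text also works arm by arm. Study endpoints lists "the number of malaria cases averted by each intervention" among the economic outcomes, and the section on economic data collection plans costs per case prevented and per DALY averted.

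Under Secondary objectives, the economic objective sets out to estimate the costs of "LLINs + IRS, LLINs or IRS alone compared to the current routine practice". It then adds an evaluation of incremental costs, effects and cost-effectiveness, without saying what they are incremental to. The entomological and hemoglobin objectives in the same list both name LLINs or IRS alone as the comparison.

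The question itself is stated elsewhere. The Background calls it important to evaluate "whether the potential extra protection gained by combining both interventions represents good value compared with the added costs" and gives the study aim as including "the cost-effectiveness of the interventions against malaria and their effect on mosquito behavior, as compared to each intervention alone". In the Abstract's Discussion, directly after a question about the combination versus either intervention alone, comes: "And is the reduced incidence justifiable compared to the added costs".

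**The concern.** A household receives routine practice, nets, spraying or both, so the arms are alternatives of which a program chooses one. The policy question is whether to pay for the second intervention where the first is already in place. That needs the difference in cost between the combination and a single intervention, divided by the difference in effect between those same two arms.

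A ratio for the combination against a common baseline blends the first component with the second. If the first is cheap for what it achieves and the second is not, the blended figure hides the poor return on the second. A program could then accept the combination at a price per case averted at which adding the second intervention would be rejected. Ranking can mislead the other way too: the arm with the lowest ratio comes first even when a program would willingly pay the higher price for the additional cases averted.

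With the comparator open, it could also be chosen after results are seen.

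**Working it through.** **What can be checked.** The article gives no unit costs, arm-specific effects, ICERs or threshold, so there is no figure to reproduce. The check is algebraic, followed by an illustration on assumed inputs.

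**Formulas.** Let C be cost and E the share of control-arm cases averted, both measured relative to control.

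- Combination against control: C(both) / E(both).
- Adding IRS to LLINs: [C(both) − C(LLINs)] / [E(both) − E(LLINs)].

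The first ratio is an average of the LLINs-alone ratio and the second ratio, weighted by share of effect. It therefore lies below the second ratio whenever LLINs alone have the lower ratio. The number of control-arm cases cancels when the two are compared, so no incidence figure is needed.

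**Assumptions (not from the documents).** Each single intervention averts 30% of cases. LLINs cost 1 unit, IRS costs 3 or 1, and the costs add. The combination removes a further 25% or 10% of the cases that remain under a single intervention. The 25% matches the effect in the Sample size section; the 10% is a less favorable case.

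- Further 25%: E(both) = 1 − 0.70 × 0.75 = 0.475; gain over a single arm = 0.475 − 0.30 = 0.175.
- Further 10%: E(both) = 1 − 0.70 × 0.90 = 0.37; gain = 0.07.

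| Assumed IRS cost | Further reduction | Both vs control | Adding IRS to LLINs | Multiple |
|---|---|---|---|---|
| 1 | 25% | 2/0.475 = 4.2 | 1/0.175 = 5.7 | 1.4 |
| 3 | 25% | 4/0.475 = 8.4 | 3/0.175 = 17.1 | 2.0 |
| 3 | 10% | 4/0.37 = 10.8 | 3/0.07 = 42.9 | 4.0 |

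**Reading the second row.** LLINs alone stand at 1/0.30 = 3.3 and IRS alone at 3/0.30 = 10.0. The weighted average checks: (0.30/0.475) × 3.33 + (0.175/0.475) × 17.14 = 8.4. Ranked by ratio, the order is LLINs, combination, IRS. For any acceptable price between 8.4 and 17.1, the combination passes when judged against control, although adding IRS to LLINs does not pass. IRS alone is dominated here, with the same effect as LLINs at three times the cost. Nothing in the stated steps would remove it. Against IRS alone the combination costs (4 − 3)/0.175 = 5.7, which looks favorable only because the reference is a dominated arm.

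**Sensitivity.** Write r for the cost of IRS relative to LLINs, e for the LLINs effect and g for the further reduction. The multiple is

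[r / ((1 − e)g)] ÷ [(1 + r) / (1 − (1 − e)(1 − g))].

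Over r from 1 to 4, e from 25% to 50% and g from 2% to 25%, it runs from 1.2 (r = 1, e = 25%, g = 25%) to 41 (r = 4, e = 50%, g = 2%). The size therefore depends almost wholly on inputs the trial has yet to supply.

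**The case against.** The strongest reply is that the document never says the ICERs will be measured against routine practice. A reader might infer this from the economic objective, but routine practice is attached there to the cost estimate, and the clause that follows promises an incremental evaluation. The Abstract and Background repeatedly give each intervention alone as the comparison, and the end of the Background lists LLINs + IRS versus each single intervention among the contrasts the four arms support. Ordering options is also the first move in a proper incremental analysis, and an article that gives the economics two sentences may have condensed the rest. Costs and effects are collected for all arms, so the right ratio can still be computed.

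Much of this stands. The text does not support saying that the plan has chosen the wrong comparator, or that dominated arms will be kept. The magnitude is an illustration, not an error found in a reported figure.

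It does not dispose of the point. A sequential analysis orders arms by cost and derives the ratios afterward; the stated plan calculates a ratio per arm and ranks on cost-effectiveness. And the economic objective, alone among the three secondary objectives, names routine practice, while the Abstract and Background ask about the single interventions. That is a divergence within the written text, not merely omitted detail.

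**Conclusion.** The point holds in a limited form. The ICER comparator is not fixed, the only one named in the economic objective differs from the one the trial's own question requires, and ranking one ratio per arm does not answer that question. The stronger statement, that the ICERs will be taken against routine practice, goes beyond the text.

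The size is unknown. On the assumptions in the table, the ratio for adding IRS to LLINs is about 1.4 to 4 times the combination's ratio against control. A material gap is plausible in this setting: the Background cites a review that found LLINs more cost-effective than IRS, and two trials in which combining them gave no significant or no added protection. The defect lies in the stated analysis and not in the data, so it can be corrected fully, preferably before results are known.

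**What to change.** Replace the ranking with a sequential incremental analysis:

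1. Order the four arms by cost.
2. Remove dominated and extendedly dominated arms.
3. Compute each ICER against the next less costly arm that remains.
4. Report LLINs + IRS versus LLINs alone and versus IRS alone as the main economic comparisons, noting where a single-intervention arm is itself dominated.
5. Keep ratios against routine practice as secondary results.

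Name these comparators in the economic objective so that it matches the Background and Abstract.

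The planned cost and effect data are sufficient. The price is a small amount of extra analysis and possibly a less favorable ratio for the combination. The effect difference between two active arms may also be smaller than that against control, so the ratio may be less precise.

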**Methods/Design:**

This 2 x 2 factorial cluster randomized controlled trial is being carried out in the Adami Tullu district in south-central Ethiopia for about 116 weeks from September 2014 to December 2016. The trial is based on four arms: LLINs + IRS, LLINs alone, IRS alone and control. Villages (or clusters) will be the unit of randomization. The sample size includes 44 clusters per arm, with each cluster comprised of approximately 35 households (about 175 people). Prior to intervention, all households in the LLINs + IRS and LLINs alone arms will be provided with LLINs free of charge. Households in the LLINs + IRS and IRS alone arms will be sprayed with carbamate propoxur once a year just before the main malaria transmission season throughout the investigation. The primary outcome of this trial will be a malaria incidence based on the results of the rapid diagnostic tests in patients with a fever or history of fever attending health posts by passive case detection. Community-based surveys will be conducted each year to assess anemia among children 5–59 months old. In addition, community-based malaria prevalence surveys will be conducted each year on a representative sample of households during the main transmission season. The cost-effectiveness of the interventions and entomological studies will be simultaneously conducted. Analysis will be based on an intention-to-treat principle.

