A 2 x 2 factorial cluster randomized controlled trial was chosen to exploit the robustness of this design to help ascertain the efficacy of the combined interventions compared to either interventions alone and the standard routine practice. This protocol was developed according to the guidelines of the Consolidated Standards of Reporting Trials (CONSORT) statement extension for cluster randomized trials [45]. The scientific value of the inclusion of the control group in this trial was also extensively debated, as it was believed that this arm allows a more reliable comparison between the groups: LLINs + IRS versus LLINs alone or control, LLINs + IRS versus IRS alone and LLINs alone versus IRS alone or control. This is the most robust design in regard to cluster randomized trials to help ascertain the efficacy of the interventions. This study design is also believed to make the results more generalizable and applicable in resource-constrained countries.

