#### Entomological study

We aim to calculate the sample size for the entomological collections based on the pilot entomological studies. In a West African study with a 90 % power and 5 % significance level, it was advised to sample eight houses from each of 15 clusters of the study arms, but the mosquito density was lower [56]. A total of 16 villages (four per arm) will be randomly selected for entomological study, in which indoor host-seeking mosquitoes will be collected by CDC light traps from four houses per arm, indoor resting mosquitoes from 16 houses per arm using pyrethrum spray collection and outdoor resting mosquitoes from four artificial pit shelters per arm of the study.

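### The mosquito-density analysis sets a four-arm ANOVA that a difference in control alone can make significant, with a two-group fallback that is not its counterpart; neither is tied to the stated comparison of LLINs + IRS with each single method

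*Protocol article*

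**What the plan says.** The Analytical plan gives one sentence on comparing mosquito densities between arms. For indoor and outdoor Anopheles it prescribes that "densities will be compared among the study arms using a one-way analysis of variance (ANOVA) if data are normally distributed or using a Mann-Whitney" comparison (the U statistic) when normality fails. It attaches no contrast or post-hoc comparison to the ANOVA and no pairs to the Mann-Whitney test.

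Control is one of the arms. The abstract states: "The trial is based on four arms: LLINs + IRS, LLINs alone, IRS alone and control". It is also sampled for mosquitoes; under Sample size, Entomological study: "A total of 16 villages (four per arm) will be randomly selected for entomological study".

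The entomological item under Secondary objectives is narrower. It asks "whether LLINs + IRS reduce entomological parameters, i.e., human biting rates, mosquito resting density, longevity, sporozoite rates". Entomological inoculation rate (EIR) completes that list, and the comparison is made "inside houses compared with LLINs or IRS", each used singly. Control is not named there.

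The Background gives a list of comparisons for the trial as a whole: "LLINs + IRS versus LLINs alone or control, LLINs + IRS versus IRS alone and LLINs alone versus IRS alone or control". It appears as part of the rationale for including a control arm.

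Under Study endpoints, EIR is the primary entomological outcome. The density measures are secondary.

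**The concern.** The two branches of the sentence test different hypotheses, and the ANOVA branch does not test the objective.

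- **ANOVA.** Its null is that all four arms have the same mean density. If LLINs + IRS, LLINs alone and IRS alone have equal densities and only control is higher, the objective's null is true and the ANOVA null is false. A significant result then shows that vector control differs from routine practice. It says nothing about adding one method to the other.
- **Mann-Whitney.** This is a two-group test, so it is not the non-normal counterpart of a four-group ANOVA and cannot compare all study arms at once. Some set of pairs must be chosen, and the sentence does not choose it.

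A check of normality would thus change the hypothesis as well as the method. Indoor and outdoor densities could end up being judged against different nulls. At stake is whether the density results answer the question posed under Secondary objectives.

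**Working it through.** The protocol states no effect size, SD or power for mosquito density, so there is no figure of its own to reproduce. The check measures how often the ANOVA is significant when the objective's null is true.

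**Inputs from the protocol.** Four arms including control; four villages per arm (Sample size, Entomological study). The two-sided 5% level is stated for the primary endpoint only and is assumed here.

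**Assumptions.** Village log densities are normal with SD 0.3, 0.5 or 0.8. The three active arms are equal. Control density is 2 or 3 times theirs.

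**Formula.** With one arm shifted by d = ln(ratio)/SD and n = 4 villages per arm, the F(3,12) statistic has non-centrality λ = n·d²·(1 − 1/4) = 3d². The ANOVA rejects when F exceeds 3.49.

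| Control vs active arms | SD | d | λ | ANOVA rejects |
|---|---|---|---|---|
| 2-fold | 0.3 | 2.31 | 16.0 | 82% |
| 2-fold | 0.5 | 1.39 | 5.8 | 38% |
| 2-fold | 0.8 | 0.87 | 2.3 | 16% |
| 3-fold | 0.3 | 3.66 | 40.2 | 99.7% |
| 3-fold | 0.5 | 2.20 | 14.5 | 78% |
| 3-fold | 0.8 | 1.37 | 5.7 | 37% |

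Simulation gives the same values to within about a percentage point. In every row the direct t-contrast of LLINs + IRS with one single-method arm (12 df) rejects in about 5%. At least one of the two contrasts is significant in about 9%, and both in about 1%.

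**Same check with a shift in SD units.** Independent normal data, only control shifted, 20,000 runs:

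- 4 units per arm: ANOVA rejects in 21%, 69% and 97% for shifts of 1, 2 and 3 SD.
- 16 units per arm (the number of spray-catch houses, treated as independent): 26%, 82% and 99% for shifts of 0.5, 1 and 1.5 SD.
- Mann-Whitney of LLINs + IRS against one single-method arm: about 3% (4 v 4) and about 5% (16 v 16), whatever control does.

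**Leaving the pairs open.** Four arms give 4·3/2 = 6 pairs. If all six were tested at 5%, the family-wise error would be about 1 − 0.95⁶ = 26% (independence approximation).

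**Cost of the direct contrasts.** Let only LLINs + IRS be lower, 3-fold, at SD 0.5. By symmetry λ is again 14.5, so ANOVA power is 78%. One unadjusted contrast has 81%, one Bonferroni-adjusted contrast about 70%, and both contrasts together about 71%.

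**The case against.** **Control does not drive both branches.** A reader might infer that a significant density result can come from control whichever test is used. The documents do not support that. A Mann-Whitney test of LLINs + IRS against LLINs alone, or against IRS alone, contains no control data and addresses the objective directly. Catches are counts, so this may well be the branch that is used. This objection stands: the control-alone problem belongs to the ANOVA only. What remains against the fallback is that it is a different kind of test and has no pairs attached.

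**The pairs are named elsewhere, and an article condenses.** The Background lists the relevant pairs for the trial, and follow-up contrasts after an ANOVA are commonly left to an analysis plan, which is not shown. So one cannot conclude that the trial will never compare the combination with each single method on density, and the absence of post-hoc detail alone would be no finding. What survives is visible in the published sentence: its main test has a null other than the objective's, and its two tests are not interchangeable. The Background list is not linked to either test and includes pairs with control.

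**The harm is not written down.** A reader might infer that a significant ANOVA will be reported as a benefit of the combination. Nothing in the protocol says so; it is a risk, not a stated intention.

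**The scenario is chosen.** Equal active arms and a 2- to 3-fold control excess are assumptions. The Study setting section reports 14% mortality of An. arabiensis to deltamethrin, the net insecticide, against 100% to propoxur, so the single-method arms may differ. Trial oversight says control residents are not prevented from obtaining nets elsewhere, which could narrow the gap. Both points limit how literally the percentages can be read. Neither makes the ANOVA null the objective's null.

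**Ranks versus means.** A rank test can accompany reported means, so that difference is a matter of preference and is not relied on here.

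**Conclusion.** The point holds in a limited form. As written, the ANOVA does not test the entomological objective and can be significant because of control alone: about 16–82% of trials with control 2-fold higher and 37–99.7% with control 3-fold higher, against about 5% for each direct contrast. These figures rest on four villages per arm, normal log densities, assumed SDs of 0.3 to 0.8 and equal active arms. The direction does not depend on them, but the size does.

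The Mann-Whitney fallback is not wrong in itself; on the right pair it would answer the question. It is not the counterpart of the ANOVA, and its pairs are not fixed where it is prescribed.

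It would also be too strong to say that direct contrasts cost no power. That is true of one unadjusted contrast (81% against 78%), but not if both must be significant (about 71%) or if each is Bonferroni-adjusted (about 70%).

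The weight is moderate to low. Densities are secondary entomological outcomes, and the sentence governs neither EIR nor malaria incidence.

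**What to change.** Replace the ANOVA/Mann-Whitney sentence with one analysis for all density outcomes:

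- a count model with a log link, arm as a four-level factor and village as the unit of inference, with no switch on a normality check;
- two named comparisons, LLINs + IRS versus LLINs alone and LLINs + IRS versus IRS alone, reported as density ratios with 95% CIs;
- a statement of whether both must be significant to claim benefit of the combination, or which multiplicity adjustment applies (without either, at least one false positive occurs in about 9% of trials);
- contrasts with control labelled secondary.

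The cost is a change of wording and slightly more analysis work; no extra mosquito collection is needed. If both contrasts must be significant, power is about 71% against 78% for the omnibus test at SD 0.5 and a 3-fold reduction. Those figures come from normal log densities with a 12-df contrast. The count model itself was not simulated, so its performance with four villages per arm should be checked when the model is specified.
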